| Exposures, Outcomes and CovariatesExposure: breast cancer Women will be considered exposed at the day of the breast cancer diagnosis (index date), denoted by the first entry of one or more of the Read codes provided in appendix 2. Primary outcomes: anxiety and depression To our knowledge, there is no validated list of Read codes to identify anxiety and depression in the CPRD GOLD primary care database. Algorithms will be developed and tested to identify anxiety and depression cases in CPRD. The algorithms will be chiefly determined by clinical diagnoses of anxiety and depression registered in the EHR with Read codes, and supplemented with information from drug prescriptions, referrals, and symptoms (if deemed suitable). Please see section N, plan of analysis for specific aim 1, for more details on the construction and validation of algorithms. Secondary outcomes: fatigue, mild cognitive impairment, pain, sleep disturbance, sexual dysfunction, and fatal and non-fatal self-harm Similarly, we will develop and test outcome-specific algorithms that identify events using a hierarchy of data on clinical diagnoses, prescriptions, referrals and symptoms.  In sensitivity analysis, we will consider linked data (see section J for data linkage requested) to develop more precise definitions of the outcomes, when possible. For example, two definitions of suicide will be considered: (1) considering Read codes only to identify suicides in CPRD; (2) considering Read codes for suicide as well as death registration data where suicide was recorded as primary cause of death (ICD-10 codes provided in appendix 3) Covariates Variables considered as potential confounders or effect modifiers of the association between breast cancer history and anxiety and depression (the primary outcomes of this study) are described below. The directed, acyclic graph (DAG) in appendix 4 explicitly describes the assumptions of the causal relations between the variables that underpin the choice. Please refer to the data analysis (section N) for details on which variables will be considered for sensitivity analyses only. *Potential confounders*  - Age at diagnosis (categorical variable, in 10-year age bands)   Defined as the absolute difference between the year of breast cancer diagnosis and year of birth. Age is a strong risk factor for breast cancer and for mental disorders.   - Alcohol drinking habits at diagnosis (categorical variable: current drinker, former drinker, never drinker)   Excess alcohol drinking is a well-established risk factor for breast cancer [30], besides being positively associated with anxiety and depression [31-33]. The most recent data on alcohol drinking habits prior to index date will be used in analysis. Current drinking will be further sub-divided into high, moderate, low or unknown intake of alcohol.   - Body mass index at diagnosis (categorical variable: underweight, normal weight, overweight, obesity class I, obesity class II and above)   Calculated as BMI=(weight/height^2^). Higher body mass index is protective against breast cancer in pre-menopausal women, but a risk factor for breast cancer post-menopause [34]. Obesity increases the risk of anxiety and depression [35, 36]. The most recent recording of BMI prior to index date will be used in analysis. The BMI values will be categorised into 5 categories: <18.5 kg/m^2^ (underweight), 18.5-24.9 kg/m^2^ (normal weight), 25.0-29.9 kg/m^2^ (overweight), 30.0-34.9 kg/m^2^ (obesity class I), ≥35.0 kg/m^2^ (obesity class II and above). Read codes for body weight categories recorded in the year prior to the breast cancer diagnosed will be considered to supplement missing information for this variable.   - Calendar period of diagnosis (categorical variable: ≤1994; 1995-1999; 2000-2004; 2005-2009; 2010-2014; >2014)   Even though calendar time *per se* does not change the risk of breast cancer, the risk of being diagnosed with breast cancer changed over time, probably due to increase awareness of the disease along with widespread use of mammography to screen for breast cancer. Time has also contributed for mental disorders being more likely to be diagnosed, due to raises awareness and increased recognition of the importance of mental disorders among health care professionals.   - Diabetes mellitus (dichotomous variable: yes/no)   Diabetes mellitus has been associated with an increased risk of breast cancer [37] and depression [38]. Algorithms previously defined elsewhere will be applied to identify patients with diabetes mellitus in the CPRD GOLD primary care database [39, 40].   - Level of deprivation (categorical variable: quintiles of patient-level IMD).   The IMD is an ecological measure of deprivation for small areas in England that combines information from seven domains (income, employment, education, health deprivation, crime, barriers to housing, and living environment), and ranks the small area from 1 (most deprived) to 32,844 (least deprived). Patients will be categorised in quintiles of IMD, with quintile 1 representing those least deprived and quintile 5 those most deprived.   - Menopausal status (dichotomous variable: premenopausal/postmenopausal)   Menopausal status is a potential confounder of the association between breast cancer history and depression, as the risk of breast cancer increases with menopause [30], and so does the risk of depression [42]. However, information on menopausal status is not easily available in the CPRD database. We will therefore produce results stratified by an age cut-off, as a proxy of the menopausal status of the women. The cut-off will be the mean/median age at natural menopause in the UK.   - Smoking history at diagnosis (categorical variable: current smoker, former smoker, never smoker)   Information on Read codes available on the data will be used to classify patients by smoking history. The most recent data on smoking prior to index date will be used in analysis. *Potential effect modifiers*  - Living alone (dichotomous variable: yes/no)   Ascertained from the CPRD GOLD primary care data using Read codes (list provided in [41]) and the patient’s family number (variable ‘famnum’ from the patient file). Women living in household of <2 people will be classified as living alone.   - Residing in a care home (dichotomous variable: yes/no).   This variable will be defined from the CPRD GOLD primary care database, using Read codes (list provided in [41]), and information gathered in the family number variable (‘famnum’). For the latter, ‘care home’ will be defined as a household with >3 individuals aged ≥65 years and if their total count was more than of individuals <65 years.   - Ethnicity (categorical variable: White, South Asian, Black, Others and mixed)   Ethnicity data recorded in the CPRD GOLD primary care database will be categorised in five groups, following the categories defined in the UK 2011 Census: White, South Asian, Black, Others and mixed. This variable will be derived from Read codes available in the CPRD GOLD primary care database and from HES, since the combined data sources increase completeness from 55% to 79% [41]. For analysis, four groups will be considered: White, South Asian, Black, Others and mixed.   - Previous mental health history (categorical variable: yes/no)   Mental health history will be defined as having had an episode of anxiety- or depression-related disorders (primary outcomes) or any the secondary outcomes, ever recorded at more than 1 year before the breast cancer diagnosis (patients who had the outcome in the year before the breast cancer diagnosis will be excluded from the cohort). These will be identified based on the algorithms defined in aim 1 of this study.   - History of stroke or coronary heart disease at diagnosis (two dichotomous variables: yes/no)   These will include ischaemic heart disease (angina and myocardial infarction) and stroke, which are amongst the leading causes of disability-adjusted life years in females in the UK. These will be identified through Read codes recorded in the CPRD GOLD primary care database.   - Socioeconomic status (IMD quintiles of deprivation)   The IMD is an ecological measure of deprivation for small areas in England (Lower Super Output Areas). It combines information from seven domain indices (income, employment, education, health deprivation, crime, barriers to housing, and living environment). The index ranks the areas from 1 to 32,844; usually the quintiles are used for research purposes: from 1 (most deprived) up to 5 (least deprived). The IMD is linked to the primary care data using the postcode of the patient or practice. *Potential mediators of the association between breast cancer history and anxiety/depression*  - Sequelae from cancer treatments (six separate binary variables (yes/no): lymphoedema, pain, mild cognitive impairment, fatigue, sexual dysfunction, sleep disorder)   Lymphoedema will be defined using Read codes for the condition, in the CPRD GOLD primary care database. Pain, mild cognitive impairment, fatigue, sexual dysfunction, and sleep disorder are secondary outcomes of this study, and will be identified based on the algorithms defined in aim 1 of this study. Patients will be classified as having had one of these conditions if there was more than one record for these conditions within a 6-month interval.   - Exposed to endocrine treatment for breast cancer: binary variable (yes/no).   This will be defined from the CPRD GOLD primary care database using Read codes for at least two prescriptions of anastrozole, tamoxifen, exemestane, or letrozole [43] within a 6-month period. |

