| Data/ Statistical AnalysisPrimary analysesSpecific aim 1. To develop and validate algorithms to identify patients with anxiety and depression Algorithm development  A systematic review is currently under way to identify the lists of Read codes previously used to define anxiety and depression of primary care databases in the UK. The systematic review search expressions are provided in appendix 5.  *(A) Raw data tabulations*  We will estimate the number and proportion of patients recorded during the observation period with:   1. Diagnostic Read code for anxiety/depression; 2. Prescription of anxiolytics/antidepressants; 3. Referred to mental health services; 4. Symptoms of anxiety/depression.   Proportions will be estimated by calendar year.  *(B) Simpler algorithm*  We will estimate the additional contribution of prescriptions, referrals and symptoms to identify cases of anxiety/depression in CPRD. Referrals and prescriptions of anxiolytics/antidepressants will be considered as sufficient to identify cases of anxiety/depression if a Read code for symptoms of anxiety/depression, respectively, were recorded during the previous year. The reasons for this are threefold: (1) there is good evidence that GPs switched from anxiety/depression diagnostic codes to symptomatic ones [44, 45], following claims of over diagnosis of these conditions; (2) antidepressants and anxiolytics have also other indications, including anxiety disorders for antidepressants [46], which raise questions of the use of these data their own to identify these outcomes; (3) pharmacological treatment of mild depression has been discouraged since 2004 [47], and thus referrals to psychotherapy may help to capture milder cases.  *(C) Complex algorithm*  A more detailed algorithm will be developed considering that some drugs are prescribed for both depression and anxiety, in addition to manage vasomotor symptoms, which may be more frequent in breast cancer survivors than in women who did not have cancer. An example for depression is given in appendix 6. We will estimate the number of patients with anxiety/depression at each step, to evaluate how much each category adds to what has been previously recorded.  Algorithm validation  A random sample of 1 million patients of both sexes will be selected from the CPRD GOLD primary care database. We will apply each algorithm and produce descriptive statistics stratified by likelihood of having the outcome, including:   - Number and proportion of patients with the anxiety, depression or both, by 3-year calendar period; - Number and proportion of patients with the anxiety, depression or both, by 3-year calendar period, age and sex; - Number and proportion of patients with the anxiety and depression by 3-year calendar period and country in the UK.   For each outcome, we will compare the estimates obtained with others obtained from the literature, prioritising national surveys of population-based data such as the following:   - Adult Psychiatric Morbidity Survey 2007 [48] and 2014 [49]; - Measuring National Well-being programme, made available by the Office for National Statistics (includes prevalence of those in the UK with some evidence indicating depression or anxiety, since 2013, by country in the UK and English regions, and by 10-year age groups up to 75 years) [50].   The final algorithm will be chosen by considering information in the numeric value closer to the estimates obtained from the literature. Sensitivity analysis Proportion estimates considering the presence of symptomatic codes within the previous year will be re-calculated to consider shorter periods of time (i.e. 3 and 6 months). Specific aim 2. Risk of mental health outcomes in women who had breast cancer compared to women who did not have cancer**Primary outcomes analysis – depression and anxiety**Main analysis Descriptive statistics including number of events observed and person-years at risk will be computed, overall and stratified by the covariates listed in section M (see above). Medical procedures for the diagnosis of breast cancer are likely to cause anxiety. To deal with this we planned to exclude patients who had a record of anxiety diagnosed within 1 year before the breast cancer; this could result in patients with higher levels of trait anxiety being excluded from the analysis. We will calculate the number and proportion of patients who were excluded because they had the outcome in the year prior to the breast cancer, stratified by month. We will also describe how many of those who were excluded from analysis had an outcome after the breast cancer diagnosis by age-group. The quintiles of the distribution of the number of consultations (defined using the ‘consid’ variable) will be described, as this can indicate the patterns of seeking care between women with a history of cancer, compared to those who did not.  The association between breast cancer history and anxiety and breast cancer history and depression, will be quantified using Cox regression models with time since index as the underlying time scale, and stratifying on matched set to account for matching by age and primary care practice. Follow up will begin at the index date (vide section M for definition of the exposure) and will terminate when an outcome is observed. Women will be censored at the earliest date of any of these: cancer recurrence, other cancer diagnosis, death, transference out of the practice; if these events don’t occur, censoring will be observed at the date of last data collection for the practice. Crude measures of the association between breast cancer history and anxiety and depression will be reported stratifying by the covariates described in section M.  Cox multivariate regression analysis will be use to estimate hazard ratios adjusted for calendar period of breast cancer diagnosis, menopausal status, and diabetes mellitus at baseline (see list of confounders in section L, covariates, for the definition of these variables).  Interaction terms between the exposure and the following variables will be added, to explore effect modification by ethnicity (White, South Asian, Black, Others and mixed), place of residence (care home vs. household), co-habitation status (living alone vs. cohabiting), SES (quintiles of IMD), having mental health disorders history (yes vs. no), having history of stroke (yes vs. no) and coronary heart disease (yes vs. no).  Confidence intervals will be calculated using robust estimates of the standard errors, to account for the fact that patients may also contribute with time at risk in the unexposed cohort prior to their cancer diagnosis.  The proportional hazards assumption will be tested in two ways: 1) graphically, by plotting the cumulative rates on a log scale; 2) inferentially, by applying a likelihood ratio test to the estimates obtained for the entire period of observation and for time split into intervals. Sensitivity analyses Sensitivity analyses planned for this study will include a subset of patients only; this is because they use variables from linked data, which is available for a fraction of the patients only, and include variables amenable to have missing data (i.e. BMI, alcohol intake, smoking and patient-level IMD). Regarding the latter, we will quantify the completeness of each variable to decide on their inclusion in the final models. Analyses including variables with missing data will be restricted to patients with complete data for covariates (complete case analysis), if missing data is likely to be missing not a random. The following sensitivity analyses are planned:   1. The main analysis will be repeated further adjusting for age at diagnosis (continuous variable, since matching allowed for 3-year gap), patient quintile level of IMD, alcohol drinking patterns prior to index date, smoking history and body mass index categories prior to index date. 2. We will exclude women diagnosed with the outcome of interest in the year prior to the cancer diagnosis. To account for the fact that treatment for these conditions may often last for more than one year, and that mild anxiety and depression may be treated in psychological services and not result in visits to the GP, we will repeated the main analysis including only patients who had 5 years of complete follow up prior to the index date and did not have the outcome recorded at any point during this period.  Multiple comparisons We acknowledge that this study includes multiple comparisons for each outcome, and several outcomes. Thus, P-values in the range ~0.01-0.05 be considered as some statistical evidence of an effect and interpreted cautiously. Sample size considerations considering a 0.01 probability of type I error (α) are provided in see section I. Specific aim 3. To estimate association between breast cancer history and anxiety/depression by presence of lymphoedema, pain, mild cognitive impairment, fatigue, sexual dysfunction, sleep disorders, and having done endocrine therapy, during the follow up period. We will estimate the cumulative incidence and period prevalence of lymphoedema, pain, mild cognitive impairment, fatigue, sexual dysfunction, and sleep disorders, in breast cancer survivors during the overall follow up period and by 5-year of follow up period.  We will estimate the hazards of developing anxiety and depression (the main outcomes) for three groups of patients: 1) breast cancer survivors who did not develop the common complication (i.e. lymphoedema, pain, mild cognitive impairment, fatigue, sexual dysfunction, sleep disorders) up to time *t*; 2) breast cancer survivors who have had the common complication at time *t*; 3) women who never had cancer. A Cox regression model will be used to estimate the association between time-updated exposure and the main outcomes (anxiety and depression), having as reference the hazard observed for the women who did not have cancer. The exposure variable will be time-updated; this means that women who develop a common complication will contribute with information to group 1 until the date at which they develop the complication of interest; after this point they will contribute with information to group 2. All models will be adjusted for calendar period of breast cancer diagnosis.  Confidence intervals will be calculated using robust estimates of the standard errors. Sensitivity analyses planned in objective 2 will be applied to this objective as well. Secondary outcomes analyses – fatigue, mild cognitive impairment, pain, sleep disturbance, sexual dysfunction, fatal and non-fatal self-harm The steps outlined above will be repeated for the secondary outcomes. Sensitivity analysis will follow the same rationale as described for the primary analysis. |

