| Limitations of the study design, data sources, and analytic methods Validity of the mental health diagnosis in the CPRD GOLD primary care database  The validity and the completeness of the recording of the mental disorders in CPRD have not been evaluated, and this will limit our results. The diagnosis and treatment of depression has also changed over time, as a result of the 2004 NICE guidelines (discouraging the treatment of mild depression with antidepressants) and the Quality and Outcomes Framework scheme in 2006, which recommended validated questionnaires to evaluate its severity [8, 9]. As for completeness, mental disorders such as depression and anxiety are managed at the primary care level, and therefore the potential for recording is high. Nevertheless, some of these conditions, especially in the sub-threshold or milder severities, may not result in GP visits and go therefore undiagnosed [10].  Unmeasured and residual confounding  This study is also limited by the lack of historical data on potential confounders, such as physical activity. Residual confounding will not be possible to rule out for variables such as smoking [53].  Multiple indications of the psychotropic medicines (complex algorithm definition)  In clinical practice, several classes of pharmacological agents are currently used to manage anxiety and depressive disorders, and many of these pharmacological agents are used to treat other physical and mental disorders (appendix 7). An example of this is illustrated by the guidelines. The National Institute for Health and Care Excellence (NICE) issued guidelines for recognition and management of depression in people who have a physical chronic condition such as cancer [54], and for management of generalized anxiety disorder (GAD) and panic disorder [46]. Low- or high-intensity psychological interventions (e.g. low intensity: individual non-facilitated or guided self-help; high intensity: cognitive behavioural therapy) are recommended as the first line for GAD, mild depression and long-term insomnia (>4 weeks) [46]. Pharmacological treatment is recommended for persisting GAD, moderate to severe depression and insomnia that causes severe daytime dysfunction. SSRI are currently recommended for GAD; benzodiazepines are most often restricted to crisis and not recommended for long-term use [46]. This will raise issues on the indication under which the patient has been prescribed the medicine. We will select all pharmacological agents used to treat each of the outcomes, and seek experts’ advice on which drugs are often prescribed. In any case, this offers a potential for misclassification (thought to be non-differential). |

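### Aim 3 can count conditions that predate the cancer as sequelae of its treatment, because the complication rule has no new-onset requirement

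*Protocol*

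**What the plan says.** The potential mediators (Protocol, Exposures, Outcomes and Covariates) include six binary conditions presented as sequelae of cancer treatment. For five of them the definition is borrowed: pain, fatigue, sexual dysfunction, mild cognitive impairment and "sleep disorder are secondary outcomes of this study, and will be identified based on the algorithms defined in aim 1 of this study". Those algorithms "identify events using a hierarchy of data on clinical diagnoses, prescriptions, referrals and symptoms". The sixth is separate: "Lymphoedema will be defined using Read codes for the condition, in the CPRD GOLD primary care database". One rule then covers all six: "Patients will be classified as having had one of these conditions if there was more than one record for these conditions within a 6-month interval".

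Specific aim 3 uses these variables to form time-updated groups. Survivors start in group 1 (no complication so far) and move to group 2, "breast cancer survivors who have had the common complication at time" t, once the complication develops. Women who never had cancer are the reference. The only adjustment named is calendar period of diagnosis. The cumulative incidence of the conditions in survivors is also to be reported.

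The exclusion criteria (Definition of the Study population) remove women with a history of the outcome in analysis during the year before diagnosis. They do not remove women with an earlier record of an aim 3 condition.

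**The concern.** Pain, fatigue and poor sleep can be present before a cancer diagnosis. If such a condition is recorded again afterwards, the written rule makes it a treatment complication. Women with long-standing pain or insomnia may also be more prone to anxiety and depression whether or not they have had cancer. Collecting them in group 2 would raise its hazard ratio, and taking them out of group 1 would lower that one, because the reference still contains women of both kinds. The result could be read as an effect of treatment complications when it reflects prior illness. The reported incidence of sequelae would be too high for the same reason.

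A second, smaller point concerns prescriptions, which may feed both the complication algorithms and the anxiety and depression algorithms. The Limitations section says "We will select all pharmacological agents used to treat each of the outcomes", and that many of the agents for anxiety and depression have other uses. No rule stops one drug from counting on both sides.

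**Working it through.** **Following one woman through the rules.** Take a survivor in the anxiety model with insomnia recorded in the 12 months before index and two further insomnia records within 6 months after diagnosis.

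- Baseline exclusion: not triggered, since insomnia is not the outcome in analysis.
- Start of follow-up: group 1.
- After the second later record: the 6-month rule is met, so she moves to group 2 and can enter the cumulative incidence.
- Adjustment: calendar period only. The previous mental health history variable does include the secondary outcomes, but it is an effect modifier in aim 2 and counts only records more than 1 year before diagnosis. It would miss her.
- Sensitivity analysis: the 5-year clean-history restriction, carried over to aim 3, also concerns the outcome only.

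**Size for the hazard ratios.** The protocol gives no aim 3 event or prevalence figures, so there is nothing to reproduce and the inputs are assumed. Let q be the prevalence of the condition before index in both cohorts and h the hazard ratio of the condition for anxiety, with no effect of cancer or treatment. The unsplit reference has average relative hazard 1 + q(h − 1). Then:

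- group 2 versus reference = h / [1 + q(h − 1)]
- group 1 versus reference = 1 / [1 + q(h − 1)]

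| q | h | Group 2 | Group 1 |
|---|---|---|---|
| 0.05 | 1.5 | 1.46 | 0.98 |
| 0.05 | 3 | 2.73 | 0.91 |
| 0.20 | 2 | 1.67 | 0.83 |
| 0.30 | 1.5 | 1.30 | 0.87 |
| 0.30 | 3 | 1.88 | 0.62 |

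For example, q = 0.20 and h = 2 give 2/1.20 = 1.67 and 1/1.20 = 0.83. The formulas take group 2 to consist of pre-existing cases that are re-recorded soon after index. Later re-recording leaves some of their time in group 1 and brings that ratio nearer to 1. New cases in group 2 would dilute the pattern.

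**Size for the cumulative incidence.** If a proportion r of the pre-existing cases have two qualifying records after index, they add q × r. With an assumed q = 0.20 and r = 0.60 this is 0.12, or 12 percentage points.

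**Why both cohorts must be treated alike.** If pre-existing cases are set apart in survivors and comparison women, the women free of the condition at index compare as 1/1 = 1.00. If they are set apart in survivors only, group 1 versus reference stays at 1/[1 + q(h − 1)], which is 0.62 to 0.98 over the same range.

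**Shared drugs.** A null simulation followed 120,000 survivors for 8 years, with no true link between sleep disorder and anxiety. Assumed rates per year were 0.01 for diagnosis, 0.05 for symptom codes, 0.03 for prescription courses (averaging six monthly scripts) and 0.03 for true complication onset. A script counted toward anxiety only with a symptom code in the previous year. A second script within 6 months was allowed to count as the complication.

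- Shared scripts not counted: rate ratio 1.04 (1,239 and 9,650 events). The standard error of the log ratio is √(1/1,239 + 1/9,650) = 0.030, so this is compatible with 1.
- Shared scripts counted: 1.20 (2,343 and 8,719 events; standard error 0.023).
- Shared scripts counted, diagnosis rate 0.005-0.02 and symptom-code rate 0.02-0.10: 1.06 to 1.65.

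The excess arises because a woman already on a shared drug becomes a case at her next script after a symptom code, while a woman not on it needs a new prescription or a diagnosis.

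**The case against.** The best reply is that aim 3 is already about new conditions. It is framed around the follow-up period, it speaks of women who develop a complication, and cumulative incidence ordinarily means first occurrence. When a condition is itself the secondary outcome in analysis, the prior-year exclusion does apply to it. This shows the likely intent. It does not say what happens to a condition recorded both before and after index in the anxiety and depression models, and the operational rule lets it in.

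On shared drugs the reply is stronger. Anxiety and depression are identified chiefly from diagnoses, and in the simpler algorithm a prescription counts only with a symptom code in the previous year. The drug lists are a product of aim 1, expert advice is planned, and the appendices with the depression algorithm and the drug table are not shown. The text does not say that a bare repeat prescription is a record of a complication. The hypnotics row in the sample size table is a power scenario. Lymphoedema uses Read codes, and overlap is plausible mainly for sleep disorder and pain. Follow-up also ends at the first outcome, so one script cannot both place a woman in group 2 and be her event; the route is a repeat course with a later symptom code. All of this stands, and it reduces the drug overlap to a possibility worth a sensitivity analysis.

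**Conclusion.** The new-onset gap holds for all six conditions. As written, a raised group 2 hazard ratio and a lowered group 1 ratio can reflect illness that predates the cancer. Under the assumed inputs the distortion runs from slight to large (group 2 from 1.30 to 2.73, group 1 from 0.62 to 0.98). The protocol holds no figures that would narrow this range.

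A reader might infer more: that the complication-outcome association is built in by shared prescriptions, or that aim 3 as a whole cannot be answered. The document does not support either. Shared drugs are possible but not stated, the outcome side is partly guarded by the symptom-code condition, and a null excess of about 1.20 in the base case rests on assumed rates and on counting bare scripts as complications. The other conditions have no shown drug overlap, and the new-onset gap can be closed with a rule.

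**What to change.** For each aim 3 condition:

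- Require first onset after index, with a stated look-back: at least the 12 months that every woman has, and longer history where available. State whether a single earlier record makes the condition pre-existing.
- Fix the onset date at the qualifying record, that is, the record that completes the 6-month rule, so that no woman enters group 2 on the strength of a later record.
- Place women with the condition before index in a separate pre-existing level, or exclude them from that condition's model, and apply the same rule to the comparison women. A separate level is simpler, because the protocol's matching rule drops the index case when a comparison woman meets an exclusion criterion.
- Compute cumulative incidence among survivors free of the condition at index.
- For sleep disorder and pain, add a sensitivity analysis that defines the complication without prescriptions of drugs that also count toward anxiety or depression.

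The cost is wording, one extra category and a restricted drug list, using data already held. Fewer complications will be counted and aim 3 will lose some precision. The change removes the pre-existing cases. It does not by itself separate a new condition's own link with anxiety or depression from that of the cancer, because the reference is not split by conditions arising in follow-up; the report should say so.
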